## Abstract

Most Indonesian gynecological cancer survivors have unmet supportive care needs during chemotherapy, which may lower their quality of life and discontinue the treatment. Digital health intervention can address this issue. This pilot investigation aims to (1) examine the feasibility and acceptability of a Fighting on distRess, Self-efficacy, Health Effects, and seXual issues (FoRSHE-X) intervention and (2) evaluate prospectively the impact of the study implementation on the level of distress, self-efficacy, side effects’ knowledge and management, and sexual quality of life using the RE-AIM (Reach Effectiveness, Adoption, Implementation, and Maintenance) framework. This is a non-randomized mixed-methods pilot study. We will recruit women diagnosed with gynecological cancer undergoing chemotherapy to participate in the FoRSHE-X intervention consisting of ten weeks of social media-based education and telecoaching. We will evaluate the primary outcomes of study feasibility and acceptability, and the secondary outcomes of study impacts at three time points with quantitative and qualitative inquiries. We anticipate a minimum of 30 participants to enroll in the study and complete the assessment. We will disseminate results through conferences and peer-reviewed scientific journals. This study will imply whether a definitive trial to evaluate the potential benefits of the FoRSHE-X is viable and how it should proceed. The protocol can aid researchers or nurses in implementing this approach in their study or practice.

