### Sampling

We will recruit participants in the DNCC’s One Day Dare Unit and inpatient units. The eligibility criteria will be (1) female aged 18 years or older, (2) being diagnosed with gynecologic cancer (including cervical, ovarian, uterine, vulvar, vaginal, and fallopian tube cancer), (3) receiving chemotherapy at the DNCC, (4) having a smartphone, (5) willing and physically or cognitively able to participate in the study and follow the study procedures, and (6) being able to communicate in Bahasa Indonesia.

On the other hand, patients diagnosed with severe neurological conditions such as unmanaged mental health diagnosis, current metastases to the brain, delirium, and dementia, as well as those with any prior history of receiving chemotherapy or cancer recurrence, will be excluded because these conditions might confound cognitive functioning [24]. Patients with severe hearing or visual impairment that would prevent them from communicating and using the educational digital material will also be excluded. Another exclusion criterion is patients who are single, divorced, or widowed with no sexual partner.

Thirty participants will be recruited using a convenience sampling technique to enroll in the study. A sample size of 30 participants is considered sufficient for evaluating the feasibility of a clinical trial and providing preliminary estimates of the effect sizes of the study outcomes [24]. Before the data collection, the participants will be provided with an explanation of the study activities and their rights, as detailed in the information sheet. The participants will be able to ask questions about any unclear aspects to the researchers and to participate in this research voluntarily. Subsequently, if a participant agrees to be involved in this study, she will sign the Informed Consent Form prepared by the study team. Meanwhile, the participant can withdraw from the study at any time.

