### Outcomes measures

#### Primary outcomes

The primary outcomes will be assessed at the end of the study period through quantitative and qualitative data collection. The data will cover participant recruitment and retention, the implementation of the intervention, and participant satisfaction.

The research team will maintain a log book to record: (1) recruitment rate: the number of gynecological cancer patients approached to participate in the study, (2) response rate: the number of patients who met the eligibility criteria and signed informed consent, (3) participation rate: the number of participant attendances in social media-based education and telecoaching sessions, (4) facilitators’ satisfaction rate, (5) participants’ satisfaction rate, and (6) attrition rate: the number of participants who received the intervention and were retained in the study until the final follow-up (week 10).

We will carry out a qualitative evaluation to assess (1) intervention adherence, (2) acceptability of the recruitment processes, intervention design and delivery, and outcome measurements, (3) barriers to recruitment and intervention delivery, and (4) participant satisfaction. Qualitative data will be collected through semi-structured interviews with the participants after the study’s completion. An experienced qualitative researcher will conduct the interviews which will be recorded using an audiotape and transcribed by a research assistant. The qualitative data collection will be terminated when the data reaches saturation.

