### Data analyses

Descriptive statistics of participants’ clinical and demographic characteristics and all study outcomes will be reported. The recruitment and retention rates will be computed to determine the feasibility of a full RCT. A future complete RCT will be deemed feasible if the recruitment rate is at least 50% and the retention rate is at least 50%. Response rates to questionnaires, follow-up rates, and intervention adherence rates will also be calculated to provide further evidence for the feasibility of a definitive RCT. For the secondary objective, we will compare the longitudinal quantitative outcomes at three-time points (before, at the middle, and after the interventions) using the paired t-test (for continuous variables) and McNemar’s test (for categorical variables), if the data are normally distributed. The non-normally distributed data will be checked using the Wilcoxon test.

Qualitative data will be analyzed using content analysis by the research team’s qualitative researchers. The team will develop a codebook based on the study objective and framework. The predetermined codes include acceptability, implementation, facilitators, barriers, and satisfaction. A qualitative researcher will code the transcripts once the final codes have been defined and agreed upon. Emerging codes can be added to the codebook during the analysis. After the analysis, a detailed description of the findings will be reported. The qualitative findings will inform the acceptability of the study and the strategies or best practices of the study protocol. All research data will be stored in a non-publicly open repository which can be accessed by the principal researcher only to protect participant confidentiality.

The core team for this research consists of nurses with expertise in cancer care. The principal investigator is a professor of nursing who will oversee the study and deliver the telecoaching intervention. The research team members include nurses working in academia and at the DNCC. The nurses at DNCC will help provide a list of patients who may be eligible. In addition, a medical oncology consultant will also be involved in the study implementation process.

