## Discussion

This study will examine whether a definitive trial to evaluate the potential benefits of the FoRSHE-X intervention that combines digital education and nurse-led telecoaching is viable and how it should proceed. Feasibility comprises the practicability of implementing the trial, including participant recruitment and retention, intervention delivery, and data collection. This study will also seek to determine appropriate and acceptable outcome measures to be included in the full RCT. As such, the intervention will be given to everyone who participated in this feasibility and pilot study. Nevertheless, using this approach, we cannot test the randomization strategy for the subsequent RCT.

The FoRSHE-X digital intervention is expected to enhance the self-efficacy of gynecologic cancer survivors in preventing and addressing communication obstacles that may hinder them from continuing therapy and preparing for the post-treatment period. This intervention can connect patients inquiring about information and psychological support from healthcare teams without space and time constraints. Digital technology is believed to expand the healthcare coverage and enhance patient participation in their sustainable self-care. The FoRSHE-X digital intervention has the potential to meet the supportive care needs of gynecologic cancer survivors undergoing chemotherapy. Therefore, the final findings of this pilot are planned to be published and disseminated to the participants, healthcare professionals, and other relevant groups. Anonymous data sets will be included in the publication.

Exploring the participants’ perspectives and experiences will also provide valuable insights into the acceptability of the study among cancer survivors who seek care. We will assess how well the FoRSHE-X intervention was received and whether participants found it suitable and beneficial. Potential challenges, uncertainties, and strategies to improve them will also be explored by the participants, including those who drop out of the study. The qualitative part of the study can also help identify other potential impacts of the intervention and its interaction with the context in which it is implemented.

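### The Abstract gives 30 as a minimum number of completers, but Sampling recruits only thirty, so 30 is the maximum and is reached only with no attrition

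*Protocol article*

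**What the plan says.** The size of the study is stated twice in the Protocol article.

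- Abstract: "We anticipate a minimum of 30 participants to enroll in the study and complete the assessment". Thirty is a minimum, and it counts women who enrol and also complete.
- Methods, Sampling: "Thirty participants will be recruited using a convenience sampling technique to enroll in the study". Thirty is the number entering. The next sentence justifies it: "A sample size of 30 participants is considered sufficient for evaluating the feasibility of a clinical trial", and for preliminary effect-size estimates, with a citation.

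The article foresees losses. Sampling notes that "the participant can withdraw from the study at any time". Primary outcomes counts the women retained to week 10. The Discussion plans to explore the views of participants, "including those who drop out of the study". Under Data analyses, one of the two conditions for calling a full RCT feasible is that "the retention rate is at least 50" per cent.

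The article states no expected retention, no over-recruitment, no replacement of women who leave, and no rule to recruit until 30 have completed.

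**The concern.** The two statements agree only if every recruited woman stays to week 10. Otherwise, what the Abstract calls a minimum is a ceiling that Sampling will not reach.

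This matters because the Abstract is where a reader looks for the size, and it has no other statement of it. The secondary objective compares outcomes across three time points with paired tests, which use only women with data at both times. Outcome measures also names the SQoL-F as the primary outcome of the future RCT, so its mean change and the SD of that change are natural planning inputs. Someone who plans from the Abstract would credit those estimates with at least 30 pairs. Under Sampling, 30 is the most there can be.

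**Working it through.** **Inputs.** Recruited: 30 (Sampling). Completers stated: at least 30 (Abstract). Lowest retention accepted by the progression rule: 50% (Data analyses). The article gives no expected retention, so the 95%, 90%, 80% and 70% rows below are assumptions that show a range. I read completing the assessment as reaching the last of the three time points, week 10.

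**Reproducing the stated figure.** No alpha, power, SD or effect size is given, so 30 comes from no formula that can be rerun. The one check available is completers = recruited × retention. Setting 30 × r = 30 gives r = 100%.

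**Completers from 30 recruits.** Expected number = 30 × r. The chance that all 30 complete, if women drop out independently, is r^30.

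| Retention r | Expected completers | Chance that all 30 complete |
|---|---|---|
| 100% | 30 | 100% |
| 95% (assumed) | 28.5 | 21% |
| 90% (assumed) | 27 | 4.2% |
| 80% (assumed) | 24 | 0.12% |
| 70% (assumed) | 21 | 0.002% |
| 50% (progression floor) | 15 | about 1 in 10^9 |

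The mismatch does not depend on the 50% figure, because any attrition leaves fewer than 30.

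**Precision of a mean change.** The 95% CI half-width, in units of the SD of the change, is t(0.975, n−1)/√n.

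- n = 30: 2.045/5.477 = 0.37 SD
- n = 15: 2.145/3.873 = 0.55 SD
- Ratio: 0.554/0.373 = 1.48, so 48% wider

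**Precision of the change-score or week-10 SD.** The 95% limits, as multiples of the observed SD, are √((n−1)/χ²) at the 0.975 and 0.025 quantiles of χ² on n−1 degrees of freedom. They assume normal data.

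- n = 30: 0.796 to 1.344, or −20% to +34%
- n = 15: 0.732 to 1.577, or −27% to +58%

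**What attrition does not touch.** The SQoL-F is also measured at baseline, so its baseline SD comes from all enrolled women with baseline data. Retention is a proportion of those enrolled, taken here as 30. At 15/30 the Wilson 95% interval is 33% to 67%, about ±17 points (exact interval 31% to 69%). Dropout is the result being measured there and does not shrink that denominator.

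**The case against.** The strongest reply is that there is no real conflict: *anticipate* expresses a hope, an Abstract condenses, and a pilot with no power claim does not depend on an exact number of completers. The primary outcomes (recruitment, response, participation, satisfaction and retention) do not need 30 completers. The article also states no confidence interval or power, so no stated precision is overturned, and a dropout allowance could sit in a full protocol that is not shown.

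Much of this stands, and it limits the point to a minor one. It does not remove the mismatch. Condensing does not turn thirty recruited into at least thirty completing, and both statements are in this article.

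Three stronger readings are tempting, and the documents do not support them.

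- *The plan expects only 15 completers.* The rule reads "A future complete RCT will be deemed feasible if the recruitment rate is at least 50% and the retention rate is at least 50" per cent. That is a threshold for progression, not a forecast. No expected retention is given, and the only stated expectation is the Abstract's own. Nor is 15 a lower bound on what could happen: fewer than 15 is the outcome in which the retention criterion fails.
- *The sufficiency claim is made for 30 completers.* In Sampling it follows directly on the thirty recruited and refers to them.
- *The SQoL-F SD in general is much less precise than it appears.* Only the week-10 and change-score SDs depend on who stays. The baseline SD does not.

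**Conclusion.** The point holds as an inconsistency in the stated size. The Abstract's minimum of 30 completers is, under Sampling, a maximum that is reached only with zero attrition. Its consequence is confined to the week-10 and change-score estimates, which are secondary. Between full retention and the lowest retention that the progression rule accepts, the half-width for a standardised mean change runs from 0.37 to 0.55 SD, and the limits for the SD of change or at week 10 run from −20%/+34% to −27%/+58%. The second figure of each pair applies only at 50% retention and should not be read as the likely result.

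This rests on reading thirty in Sampling as the total recruited with no replacement, which is all the article describes. The progression rule and the primary feasibility outcomes are unaffected. Severity: minor.

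**What to change.** - In the Abstract, say that 30 participants will be enrolled, and drop the minimum for completion. If a replacement rule does exist in the full protocol, Sampling should state it.
- In Sampling, add that week-10 and change-score estimates will rest on fewer women than were enrolled. Give their precision as the range above, with 15 completers labelled as the lowest yield that the progression rule accepts and not as an expected number.
- State that the baseline SD and the retention rate are estimated from all enrolled women, with a 95% CI for retention of about ±17 points if it is 50%.

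The cost is a few sentences. No added enrolment is proposed, and neither the progression rule nor the analysis changes. The one drawback for the authors is that the implied precision of the later estimates will look less favourable.

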**Trial registration: Clinical trial registration number:**
ISRCTN13311651.

## Introduction

Cancer is the second leading cause of mortality in the world, with 10 million cancer-related deaths estimated to occur in 2020 [1]. According to the World Health Organization (WHO), low- and middle-income countries (LMICs) bear the most tremendous burden of cancer [2]. More than 70% of the 10 million cancer-related fatalities were in LMICs [2]. In the case of cervical cancer, the disparity is even more prominent, as 90% of new cases and deaths happened in LMICs [1]. Other gynecological cancer types, including ovarian and uterine corpus cancer, also contribute significantly to the burden of cancer in LMICs [1].

Given the immense cancer concerns in many LMICs, reducing premature mortality through promoting well-being has been listed as one of the targets (target 3.4) of the Sustainable Development Goals (SDG) [3]. Therefore, increasing the country’s capacity to provide quality care across the cancer care continuum, including survivorship care, is necessary. Although cancer has been set among the top national catastrophic diseases to prioritize in Indonesia, survivorship care is still suboptimal [4].

An individual can be considered a cancer survivor at the time of diagnosis through the remain of his or her life [5]. Earlier studies showed that most Indonesian gynecological cancer survivors had unmet needs, especially regarding information and comprehensive care [6, 7]. The survivors reported that they hardly had enough time and opportunity to discuss with the health providers, particularly the nurses, the physical, psychosocial, sexual, and other issues that arose during and after cancer therapy [6–8]. The availability of cancer survivorship educational media in Bahasa Indonesia is low, and most Indonesian cancer survivors also have inadequate health literacy [9]. These conditions might hamper the continuity of care and lead to an unanticipated relapse [10]. In addition, unmet needs were also found to be linked to the low quality of life of gynecological cancer survivors in Indonesia [11].

In the digital era, many digital devices and platforms, including mobile phones, mobile applications, websites, and wearable devices, are increasingly used in healthcare services [12]. Digital technologies can be harnessed to enhance communication between cancer patients and healthcare providers [13]. Indeed, prior systematic reviews showed promising findings of the digital interventions’ effects in addressing cancer survivors’ unmet health information needs and physical and psychosocial support [14–17]. The interventions were delivered through, for instance, social media, messaging, or video-conferencing to connect cancer patients with their health providers, enhance their positive health behaviors, and complete their treatment. Digital interventions can serve as an excellent means to assist cancer survivors in managing their disease and treatment side effects, thereby improving their quality of life and the continuity of the therapy [14, 17, 18]. Digital health interventions were also found to be as effective as usual care to improve the quality of life among cancer survivors [18]. Given their broad potential benefits, the WHO has recommended using digital technologies to strengthen the national health system and achieve the vision of health for all [12].

Nursing intervention for gynecological cancer survivors has not yet been well developed to provide comprehensive and culturally sensitive services in Indonesia, incorporating new technology. Gynecological cancer survivors undergoing cancer therapy will have a better prognosis if they can complete their treatment and understand health management during chemotherapy. Throughout therapy, gynecological cancer survivors have multidimensional needs that, if not well anticipated, may result in therapy termination, relapse, or even death [19]. These needs encompass prevention of recurrence, adopting a healthy lifestyle, managing physical symptoms arising from cancer and its therapy, managing psychosocial and sexual issues, and obtaining information related to self-care [20, 21].

We are developing a sustainable intervention that embraces digital technologies to overcome the communication barriers between cancer survivors and healthcare providers and to improve self-management for the physical, mental, social, and sexual effects of chemotherapy in the patient’s life. We aim to leverage a digital health intervention to address the insufficiency of survivorship care for Indonesian gynecological cancer survivors by combining social media-based education and telecoaching. Therefore, we propose a digital solution called Fighting on distRess, Self-efficacy, Health Effects, and seXual issues (FoRSHE-X).

We will conduct a study to examine the feasibility of the FoRSHE-X intervention using the RE-AIM (Reach, Effectiveness, Adoption, Implementation, and Maintenance) Framework with the specific primary objectives as follows (1) to examine the eligibility and acceptability of the participants towards the study intervention, (2) to evaluate the feasibility of digital education, telecoaching, and intervention facilitators, (3) to evaluate the process of the implementation, and (4) to evaluate the intervention sustainability or participants’ involvement over time. Additionally, the secondary objective is to evaluate the impact of the pilot study on the level of anxiety, self-efficacy, side effects’ knowledge and management, and sexual quality of life and the participants’ perspectives towards this study intervention.

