## Methods

### Design plan

We will conduct a non-randomized mixed-methods pilot and feasibility study in which all participants will receive the FoRSHE-X intervention. We will adapt the RE-AIM Framework of O’Brien and colleagues [22] to evaluate the feasibility and pilot study (Table 1). The RE-AIM dimensions represent multiple tasks of complex multi-component intervention [22]. This feasibility study asks questions: Can a definitive trial to assess the effect of an intervention be conducted? Should we proceed with it, and how? [23]. A pilot study is a subset of a feasibility study in which the future trial is entirely or partially performed on a smaller scale [23]. Quantitative and qualitative approaches will be used to achieve the study objectives.

**Table 1 pone.0299901.t001:** Defining objectives and data collection using RE-AIM framework.

RE-AIM Dimension	Objectives	Quantitative Data	Qualitative Data
**Reach**	To examine the eligibility and acceptability of the participants.	Demographic and clinical data	Participants’ experience and perspective on the acceptability of the recruitment process and involvement in this study.
		Acceptance of the research invitation	Facilitators’ concerns and challenges in recruiting potential participants.
**Effectiveness**	To evaluate the impact of the intervention outcomes.	Chemotherapy side effects	Participant’s experience and perspectives on the effect of FoRSHE-X intervention on their health.
		Self-efficacy	
		Distress Thermometer	
** **		SQoL-F	
**Adoption**	To evaluate the feasibility of digital education, telecoaching, and intervention agents.	Complete response to the questionnaire	Researcher daily memoing
		Facilitators satisfaction	Facilitators’ experience with digital education and telecoaching.
**Implementation**	To evaluate the process of implementation (usability).	Coaching log book	Participants desire and challenges to follow the intervention.
		Proof of telecoaching attendance	
**Maintenance**	To evaluate the intervention sustainability or participants’ involvement over time.	Participant’s diary notes	Participant’s experience and perspectives towards digital education and telecoaching activities.
		Participant’s adherence on telecoaching	
		Follow-up rate	
		Participant retention	

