### Study settings

The study will be initiated at the Dharmais National Cancer Center (DNCC) in Jakarta, Indonesia. It is a comprehensive cancer center providing cancer care, education, research, and data in Indonesia. As a national referral hospital, it serves as the central hub for cancer diagnosis, treatment, and management, serving patients from Jakarta and nationwide. DNCC offers chemotherapy in several units, including the Systemic Therapy Unit, One Day Care Unit, and Inpatient Unit, in which the potential participants will be recruited, informed about the study, and signed the research consent. Then, the overall study activities will take place online. Digital assessment forms and educational materials are prepared to be accessed by the participants from their homes.

The core team for this research consists of nurses with expertise in cancer care. The principal investigator is a professor of nursing who will oversee the study and deliver the telecoaching intervention. The research team members include nurses working in academia and at the DNCC. The nurses at DNCC will help provide a list of patients who may be eligible for this study. In addition, a medical oncology consultant will also be involved in the study implementation process.

The protocol of this study has been approved by the Ethics Committee of Nursing Faculty, Universitas Indonesia (Approval number: KET-136/UN2.F12.D1.2.1/PPM.00.02/2023) on 29^th^ May 2023 and the committee of the Medical Research Ethics of the Dharmais Cancer Hospital (Approval number: 259/KEPK/VIII/2023) on 8^th^ August 2023. The ISRCTN registry had reviewed and registered this trial (ISRCTN13311651) on 11^th^ March 2024. Any changes or modifications to the protocol before or during the study data collection will be informed to the ethics committee, research team, and the participants if needed.

The participants’ recruitment will be initiated in October 2023 and is scheduled to be terminated in June 2024. Then, evaluation and data analysis of the study outcomes will be performed from July to September 2024.

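### Eligibility is part of primary objective 1, but the listed log book counts cannot give the eligible share or show which criterion limits reach

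*Protocol article*

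**What the plan says.** The Introduction gives the first primary objective as "to examine the eligibility and acceptability of the participants towards the study intervention". Table 1 (Methods, Design plan) restates it for the Reach dimension: "To examine the eligibility and acceptability of the participants". The quantitative data assigned to that row are demographic and clinical data and "Acceptance of the research invitation". The qualitative data are participants' views on recruitment and involvement, and the facilitators' concerns and difficulties in recruiting.

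On where candidates come from, Study settings says: "The nurses at DNCC will help provide a list of patients who may be eligible for this study".

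Primary outcomes numbers six log book items. The first is "recruitment rate: the number of gynecological cancer patients approached to participate in the study". The second is "response rate: the number of patients who met the eligibility criteria and signed informed consent". The other four concern attendance, facilitator satisfaction, participant satisfaction and attrition.

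The qualitative evaluation in the same section is to cover "barriers to recruitment and intervention delivery", among other topics. The collection method is described as follows: "Qualitative data will be collected through semi-structured interviews with the participants after" the study ends. The Discussion adds that women who drop out will also be heard.

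Data analyses sets the progression rule: a full RCT is deemed feasible if recruitment and retention each reach 50%.

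**The concern.** An objective about eligibility needs at least a count of people assessed and a count of those found eligible. The listed items supply neither. Recording begins after some patients have already been set aside in drawing up the list, and the only count that mentions the criteria also requires a signed consent form.

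This matters because several criteria under Sampling could be restrictive: a smartphone, no earlier chemotherapy or recurrence, and the exclusion of women who are single, divorced or widowed with no sexual partner. Which of these shrinks the pool most, and by how much, is what the planners of the definitive trial need to know when they choose the number of sites and decide whether to relax a criterion. What is not logged while recruitment runs is hard to reconstruct later.

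A related weakness affects the barriers to recruitment. Enrolled women, including later dropouts, got past those barriers. Facilitators can report what they saw. Women who refused are not named as a source, and no log item records a reason for refusal.

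**Working it through.** The plan states no figure on this point, so there is nothing to reproduce. The check asks what the listed counts can identify.

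**Inputs.** From the article: 30 participants (Sampling), recruitment from October 2023 to June 2024, nine months (Study settings), and a 50% recruitment threshold (Data analyses). The number approached, the clinic pool, the acceptance rate and the size of the later RCT are not given. All values used for them below are assumptions. The log book defines the recruitment rate as a bare count, so I take the rate to be signed divided by approached.

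**Step 1: among those approached.** The two logged counts give

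signed / approached = (eligible / approached) × (signed / eligible).

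Only the left side is observed. With 30 signed, the number eligible lies between 30 and the number approached.

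| Approached (assumed) | Signed / approached | Possible eligible share | Matching consent among eligible |
|---|---|---|---|
| 40 | 30/40 = 75% | 75% to 100% | 100% to 75% |
| 60 | 30/60 = 50% | 50% to 100% | 100% to 50% |
| 100 | 30/100 = 30% | 30% to 100% | 100% to 30% |

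For 60 approached, an intermediate case is 45 eligible: 45/60 = 75% eligible and 30/45 = 66.7% consenting. The logged counts are the same in every case within a row.

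**Step 2: before the approach.** Keep 60 approached and 30 signed, and let the clinic pool behind the list be 60, 120 or 240. Enrolment as a share of the pool is 30/60 = 50%, 30/120 = 25% or 30/240 = 12.5%. The recruitment rate is 30/60 = 50% each time and just meets the threshold.

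**Step 3: what this means for planning.** Assume the list is accurate, so that everyone approached is eligible, and that 60% accept. The threshold is passed. Enrolling 30 takes 30/0.60 = 50 eligible women.

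- If 60% of clinic patients are eligible: 50/0.60 = 83 patients, or 83/9 = 9 per month.
- If 15% are eligible: 50/0.15 = 333 patients, or 333/9 = 37 per month.

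For an assumed RCT of 200, 200/0.60 = 333 eligible women are needed. That means 333/0.60 = 556 or 333/0.15 = 2,222 clinic patients. The listed counts do not separate the two cases.

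**Step 4: sources on barriers.**

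| Source | Planned? | Where |
|---|---|---|
| Women who completed | Yes | Primary outcomes |
| Women who dropped out | Yes | Discussion |
| Facilitators | Yes, with no collection method described | Table 1, Reach |
| Women who declined | Not named | – |
| Women found ineligible | Not named | – |

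**The case against.** Five points can be made in defence of the plan.

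*Barriers to recruitment are covered.* A reader might infer that they cannot be learned at all. The documents do not support that. The Reach row plans facilitators' accounts of recruiting difficulties and also records acceptance of the invitation. Staff who met refusals are therefore a source, though a second-hand one.

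*Objective 1 can still be answered.* A reader might infer that the whole objective fails. It does not: its acceptability part has quantitative and qualitative measures. Only the eligibility part lacks one.

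*The objective may mean less.* It speaks of the eligibility of participants, not of a proportion of all chemotherapy patients, and Table 1 gives its own data for it. That is fair as a matter of wording. But every enrolled participant is eligible by definition, so describing them cannot examine eligibility in any informative sense.

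*An article condenses.* A screening log may exist in the full protocol, and the nurses' list is not said to be the only route to candidates. It would be wrong to conclude that no screening records are kept. What stands is that the article lists its log items one by one and maps data to each objective, and neither place contains a measure of eligibility.

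*Accrual is observable.* Thirty consents over nine months give 30/9 = 3.3 per month at this centre, if recruitment fills the window. That is useful, although convenience sampling to a fixed target weakens it. It does not show whether the limit is eligibility, willingness or staff effort. The calculation in Step 3 also lets clinic volume vary, so it shows what is unidentifiable and does not forecast anything.

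**Conclusion.** The point holds as a mismatch between a stated primary objective and the measures listed for it. Eligibility is to be examined, but the counts begin at approach and merge eligibility with consent. Neither the eligible share nor the limiting criterion can be derived from them. The recruitment threshold does not protect against this. Read as signed over approached, it constrains eligibility among those approached but says nothing about the share of the clinic that could be approached.

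On barriers to recruitment the plan is limited, not empty: accounts will come from enrolled women and facilitators, and not from women who declined.

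The size cannot be stated from the article. Under the assumed inputs, identical logged counts are compatible with a fourfold difference in the underlying pool (60 against 240, or 83 against 333). The conclusion itself depends on no assumed number. It rests on taking the article's numbered log items as the counts that will be kept. The gap deserves correction because it bears on the pilot's own question of how to proceed to a definitive trial.

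**What to change.** Start the log at every woman with gynecological cancer receiving chemotherapy in the recruiting units during the recruitment period. Name those units: Study settings lists three and Sampling mentions two types, and the denominator depends on which apply.

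Keep one de-identified line per woman:

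- each eligibility criterion met or failed;
- approached or not;
- consented or declined;
- any reason for declining that she volunteers.

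Report screened, eligible (with exclusions by criterion), approached and consented as four separate counts. Make eligible divided by screened the Reach measure of eligibility. Use the reasons for declining alongside the facilitator and participant accounts when describing barriers to recruitment.

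The cost is modest extra record-keeping by nurses who already help compile the list, and a notification to the ethics committee, for which Study settings already provides. No visits or participants are added. Volunteered reasons will be incomplete, so they should be reported with the number of women who gave none.
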